### Response criteria

Criteria for AML and ALL: Includes complete response (CR), partial response (PR), transient response, treatment failure, treatment failure due to patient death, and relapse [26] (Table 4). Response Criteria for Lymphoma: Includes CR, PR, stable disease (SD), relapsed disease or progressive disease (PD) [27] (Table 4).

**Table 4 T4:** **Response criteria for cellular immunotherapy in both leukemia and lymphoma [**[26]**,**[27]**]**

	**AML/ALL**	**Lymphoma**
Complete Remission (CR)	• No leukemic blasts in PB	Nodal
	• No extramedullary leukemia	• If PET positive prior to treatment then any mass provided PET negative. If PET negative or variably positive then nodal regression to normal size on CT
	• BM cellularity > 20% without Auer rods and <5% blasts	
	• ANC > 1.0 × 10^9^/L	Spleen/Liver
	• Platelet count > 100x10^9^/L.	• Not palpable, resolution of nodules
		Bone Marrow
		• Morphological clearance or if morphology equivocal then IHC normalization
Partial Remission (PR)	• All criteria for CR except bone marrow may have 5-20% blasts	Nodal
		• ≥ 50% decrease in the SPD of up to 6
		• largest masses
		Spleen/Liver
		• ≥ 50% decrease in SPD of nodules if multiple nodules, ≥ 50% in size of the transverse diameter of a single nodule if solitary mass
		Bone Marrow
		• No new bone marrow involvement
Transient Response (TR)	• Loss of PB blasts	N/A
	• >50% reduction in BM blasts	
Stable Disease (SD)	N/A	• If PET positive pretreatment, then PET positive post treatment at previous sites. If PET negative pretreatment then no CT change in size of previous lesions.

### Statistical considerations

As noted above, the safety of cellular therapy administration in the first six patients will be reviewed by the FDA and the BrUOG Data Safety Monitoring Board (DSMB). These reviews will be shared with our institutional IRB. If the treatment appears safe, as determined by the FDA and the BrUOG DSMB with institutional IRB agreement, the protocol may be reopened to treat a total of 25 patients. A sample size of 25 patients will differentiate between a 10% level of activity and a 30% level of activity. Specifically, the hypothesis to be tested is:

H_0:_ p< 0.1 versus H_1_: p> 0.3

A Simon two-stage design will be used in this study. The first 15 evaluable patients will be assessed for activity. The trial will be terminated early if activity is observed in 0 or 1 of these 15 patients, and it will be concluded that the true activity rate is unlikely to be > 10%. If activity is demonstrated in at least 2 patients, accrual will continue until a total of 25 evaluable patients are enrolled. If activity is observed in 5 or fewer of 25 patients, the null hypothesis will be accepted and it will be concluded that there is not sufficient activity to merit further investigation of the regimen. Otherwise, it will be concluded that the treatment regimen has sufficient activity to warrant further investigation.

The characteristics of this study design are as follows:

This design yields a type I error rate of <0.05 (α=0.03) and power of 80% when the true response rate is 30%.

Overall survival, time to progression, and progression free survival will be determined by the Kaplan Meier method (from the time of study enrollment).

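### Stopping on 0 or 1 responses in 15 does not support the stated conclusion that the true rate is unlikely to exceed 10%; it argues against a rate of 30% or higher

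*Protocol article*

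**What the plan says.** All of the relevant text is in the protocol article under Statistical considerations. The aim is stated as "A sample size of 25 patients will differentiate between a 10% level of activity and a 30% level of activity", with the hypotheses given as "H_0:_ p< 0.1 versus H_1_: p> 0.3". The method is named: "A Simon two-stage design will be used in this study".

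At stage 1, "The first 15 evaluable patients will be assessed for activity". The futility rule reads "The trial will be terminated early if activity is observed in 0 or 1 of these 15 patients", and the inference attached to it is "it will be concluded that the true activity rate is unlikely to be > 10" per cent. With two or more responses, "accrual will continue until a total of 25 evaluable patients are enrolled". At the end, five or fewer responses in 25 lead to acceptance of the null hypothesis and a finding that activity is too low to pursue. Six or more lead to the opposite finding. The stated error rates are a type I error of 0.03 and a power of 80% at a true rate of 30%.

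**The concern.** The stage-1 sentence is a statement about the true rate, fixed in advance, and the article gives no other efficacy conclusion for a trial that stops at 15 patients. To say that rates above 10% are unlikely, the stopping outcome would have to be improbable whenever the true rate is above 10%. A bound of 1 in 15 is not built for that. It is set so that a treatment with a 30% rate is seldom discarded. The sentence therefore names the null rate where the evidence bears on the alternative rate.

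What is at stake is the reported conclusion in one of the design's three pre-specified outcomes (stop at stage 1, accept the null at the end, declare sufficient activity). The decision to stop is not in question.

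**Working it through.** **Inputs**, all from Statistical considerations: p0 = 0.10, p1 = 0.30; n1 = 15, stop if X1 ≤ 1; n = 25, reject the null if the total is 6 or more.

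**Step 1: reproduce the plan's own figures.** The probability of rejecting the null at a true rate p is

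Σ over x = 2 to 15 of P(Bin(15, p) = x) × P(Bin(10, p) ≥ 6 − x).

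- At p = 0.10 this is 0.0328, which agrees with the stated 0.03.
- At p = 0.30 it is 0.8017, which agrees with the stated 80%.

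A search over two-stage designs with type I error at most 0.05 and power at least 0.80 also finds these bounds as the Simon minimax design. The design figures are right.

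**Step 2: how likely is the stopping outcome at each true rate?**

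P(X1 ≤ 1) = (1 − p)^15 + 15p(1 − p)^14.

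| True rate | P(0 of 15) | P(1 of 15) | P(stop) |
|---|---|---|---|
| 10% | 0.206 | 0.343 | 0.549 |
| 15% | 0.087 | 0.231 | 0.319 |
| 20% | 0.035 | 0.132 | 0.167 |
| 25% | 0.013 | 0.067 | 0.080 |
| 30% | 0.005 | 0.031 | 0.035 |

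(Components are rounded separately, so a row may differ from its total in the last digit.) The stopping probability is 0.050 at p = 0.279. With a true rate twice the null rate, about one trial in six would stop and report that a rate above 10% is unlikely. At 15% it would be about one in three.

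**Step 3: exact upper limits after stopping.**

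- 0/15: the one-sided 95% limit solves (1 − p)^15 = 0.05, so p = 1 − 0.05^(1/15) = 0.181. The two-sided 95% upper limit is 1 − 0.025^(1/15) = 0.218.
- 1/15: the one-sided 95% limit solves (1 − p)^15 + 15p(1 − p)^14 = 0.05, so p = 0.279. The two-sided 95% interval is 0.2% to 31.9%.

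Both one-sided limits lie well above 10%. Both lie below 30%.

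**The case against.** The best case for leaving the text alone is that nothing operational depends on it. The same data would stop the trial however the sentence is worded, and readers familiar with two-stage designs may take it as shorthand for not rejecting the null. The observed rate would also be at most 1/15 = 6.7%, below 10%. The first point stands, and it limits the matter to interpretation. The others do not rescue the sentence. Failing to reject a rate of 10% is not evidence against rates above 10%, and a point estimate from 15 patients carries the uncertainty shown in the working.

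One could instead read *unlikely* as a posterior probability. The article gives no prior. With a uniform prior, the probability that the rate exceeds 10% is 0.51 after 1/15 and 0.19 after 0/15. With a Jeffreys prior it is 0.38 and 0.07. Only 0/15 under the second prior comes near the claim, and the sentence covers both counts.

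Three stronger readings are tempting, and the document does not support them.

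- A reader might infer that the hypotheses are mis-set because the strict inequalities leave out 10% and 30%. This is notation only. The rejection probability rises continuously with p, so the largest type I error over rates below 10% is still 0.0328 and the smallest power over rates above 30% is still 0.8017. The text also names both design rates plainly.
- A reader might infer that this sentence closes off activity between 10% and 30%. That follows from the choice of 10% against 30% and from the bounds. Rewording the conclusion would not keep the trial open.
- A reader might infer that stopping speaks against a 30% rate and nothing lower. That describes the bound of 1/15. A count of 0/15 also makes rates above about 18% unlikely on a one-sided 95% basis.

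**Conclusion.** The conclusion attached to stage-1 stopping is wrong as written, and nothing else in the article corrects it. Stopping is more likely than not at a true rate of exactly 10% (0.55) and remains common at 15% (0.32) and 20% (0.17). It becomes improbable at the 5% level only from about 28% upward. The supportable statement is that a true rate of 30% or higher is unlikely.

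That statement rests on the stopping probability of 0.035 at 30%, or equally on the one-sided 95% exact limit, which matches the one-sided test. It should not be tied to the two-sided 95% interval, because for 1/15 that interval reaches 31.9% and so contains 30%.

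The calculations assume 15 independent evaluable patients with a common response probability, as the design itself does. The error is confined to interpretation. Stopping bounds, sample size, type I error and power are unaffected.

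**What to change.** Replace the conclusion in the stage-1 stopping rule with wording such as: *a true activity rate of 30% or higher is unlikely (0 or 1 response in 15 has probability 0.035 at a 30% rate), and activity is not sufficient to continue the trial*. Report with it the one-sided 95% exact upper limit for the observed count: 18.1% for 0/15 or 27.9% for 1/15. Naming the one-sided basis keeps the sentence and the reported limit consistent.

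No change is needed to the bounds, the sample size, the error rates or the way the hypotheses are written. The cost is one sentence of text and a slightly less sweeping negative conclusion if the trial stops early.

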## Translational endpoints

### Prospective studies for evaluation of donor and patient alloreactivity

Within our center we have created an *in vitro* study in which inactivated randomly selected mismatched donor cells are mixed with CD3+ cells from leukemia patients. Stimulated CD3+ patient cells are then placed on ^51^Cr labeled leukemic blasts with cytolytic activity measured by ^51^Cr release. Preliminary results obtained thus far show cytolytic anti-leukemic activity in approximately half of the stimulated patient CD3+ cells [28]. Because these results are about the same frequency as the responses to cellular immunotherapy, it raises the question of whether this *in vitro* assay would be predictive of *in vivo* responses using the donor/patient combination to be tested. Further, if CD3+ proliferation and cytolytic activity, as determined by *in vitro* assays, is donor dependant then it may be possible to identify an optimal donor. These *in-vitro* studies will be done in a prospective manner by obtaining additional tubes of blood from patient and donor at the day −28 time point (Figure 1). Blood will also be obtained from other individuals that could have been considered as donors or from completely mismatched normal controls.

CD3+ cells from recipient peripheral blood mononuclear cells (PBMC) will be positively isolated using immunomagnetic particles from Miltenyi Biotec^©^. Mitomycin C treated PBMC from donors (stimulators) will be placed in a mixed lymphocyte culture (MLC) with recipient CD3+ cells (responders). CD33/CD34+ cells from Recipient CD3- fraction will be positively selected with immunomagnetic particles from Miltenyi Biotec to create a blast target population for cytolytic studies. MLC proliferation assays will be measured on day 5. On day 7, MLC cells will be collected. Recipient CD33/34+ blasts will be labeled with ^51^Cr MLC stimulated cells will be co-cultured with ^51^Cr labeled blasts for cytolytic assays. The ability to induce the patient’s CD3+ cells to generate anti-leukemic effector cells using the different stimulator cells will be compared to the clinical results subsequently seen in the patient.

### Identification of functional effector cells after cellular infusion

Blood samples will be taken frequently during the first few days after cellular infusion (Figure 1). Blood will be centrifuged with the plasma collected from these samples and aliquots frozen down for future analysis. PBMC will be isolated from the cell pellet using Ficoll-Hypaque discontinuous centrifugation. An aliquot of PBMC will be frozen down for killer-cell immunglobulin like receptor (KIR) expression using Luminex based typing (Gen-Probe) [29]. PBMC analysis will include cell staining for the presence of various subpopulations and their activation status. A panel of anti-HLA antibodies coupled with AlexaFluor 488 that has been shown to be useful for detecting microchimerism during pregnancy in 90% of individuals tested has been made available [30,31]. These antibodies will be used to distinguish donor and recipient cells. In addition to determining the percentage of donor cells circulating in the blood at these different time points, these antibodies can be combined with antibody staining panels that define different subpopulations (CD3, CD4, CD8, CD56, CD69), as well as cytokine and granzyme production by these cells. If there are sufficient cells, it may be possible to use antibody panel staining with anti-HLA antibodies to sort for donor and/or recipient cells. Once collected, these populations could be tested directly for their ability to lyse leukemic target cells or natural killer target cells such as K562. If there are limited number of cells, PCR will be performed to determine the expression of loci expressing effector molecules.

### Identification of cytokine, chemokine, and granzyme profiles and extracellular vesicle release patterns

Cytokine (IL-2, IL-4, IL-6, IL-10, IL-12, IL-15, IL-18, IL-21, IFN γ), chemokine (MCP, MIP1b, CX3CL1) and granzyme (A, B) levels present in the plasma will be determined using multiplex assays (CBA flex set assays or Luminex assays) using the same blood samples obtained for effector cell analysis (Figure 1). In addition to cytokine profiles, patient plasma samples will be examined for extracellular vesicle content. Vesicles will be isolated by ultracentrifugation and examined for protein and RNA content.

## Discussion

Cellular Immunotherapy for Refractory Hematological Malignancies provides a novel treatment for patients with relapsed and refractory acute leukemia or aggressive lymphoma. We believe this therapy could offer the immunological benefit of bone marrow transplantation (i.e. GVL) without the deleterious effects of myeloablative conditioning regimens and the risk of GVHD. Although the exact mechanism of action behind the clinical efficacy remains to be elucidated, we believe that the potential therapeutic benefit is too great to ignore. Furthermore, laboratory correlative studies will be performed in conjunction with the clinical trial. This provides a true bench-to-bedside approach that should serve to further enrich knowledge of host tumor tolerance and mechanisms by which this may be overcome.

The overriding goal of this phase I/II study is to generate clinical responses with a treatment that is safe and well tolerated. The initial six patients enrolled will be re-evaluated for safety considerations with potential alterations to the protocol made in order to enhance both safety and efficacy. The purposeful rejection phenomenon seen within our study could serve as a platform for additional trials of host-mediated immunotherapy for other malignancies.
